### Training for Facilitators

All facilitators will take part in a virtual training session individually or in a group. The content of the AIM intervention was developed by LW, CM, and HH. A slideshow was developed by LW and provided to the rest of the study team for review. The slides were then translated to French to provide the training to francophone facilitators. Given that New Brunswick is a bilingual province, the research team wanted to ensure that we could recruit both anglophone and francophone participants in all regions in the province. The research coordinator scheduled the training sessions and provided a copy of the slides to the trainees before their scheduled training session. Textbox 2 provides an overview of the content that was included in the training slideshow.

Facilitator training content.
**Section 1: an overview of the advocacy intervention for midlife and older women (AIM) study**
Study rationaleStudy goal and research questionsEmpowerment componentSocial support componentTasks to be completedEligibility criteria for participantsStudy timelineResearch team members
**Section 2: diverse midlife and older women and intimate partner violence**
Applying an intersectional lens to violence against midlife and older womenIntersectionality wheelUsing a trauma-informed approachWheels of power and controlWarning signs that an older adult may be in an unhealthy relationshipWorking with rural women who are in midlife and olderWorking with Black women who are in midlife and olderWorking with midlife and older women who are immigrantsWorking with midlife and older women who are francophone
**Section 3: safety planning for older women**
Safety planning toolkitDigital safety strategies: computer safetyDigital safety strategies: cell phone safety
**Section 4: local community and legal resources**
National resourcesNew Brunswick resourcesNova Scotia resourcesPrince Edward Island resources
**Section 5: supporting midlife and older women to develop goals and strategies for the future**
Using specific, measurable, achievable, relevant, time-bound (SMART) goals
**Section 6: documenting the delivery of the AIM program**
Plans for documenting sessions with participants on the study’s OneDrive

LW will be delivering the training session along with the research coordinator who will be present to answer any questions about the study procedures. The research coordinator will be responsible for communicating with the facilitators for the duration of the study. The training session was not designed to be a lecture but rather to share information and to have an open dialogue with the service providers who already have a great deal of experience providing services to clients. The training session was used to ensure that facilitators were informed on how to deliver the components of the AIM intervention in a highly individualized way. Facilitators were also encouraged to contribute to the list of resources provided if they had knowledge of other resources in their region that were not listed. Facilitators were informed that they could begin recruiting participants upon completion of the training session.

### Random Assignment of Interventions

REDCap (Research Electronic Data Capture; Vanderbilt University) software will be used to store and manage the data collected from participants. REDCap is a web-based software application that securely stores research data [42]. The random allocation sequence was generated using REDCap [42]. The research coordinator developed an allocation table that included each option for random assignment that was stratified by the province of residence. This involved creating an Excel (Microsoft Corp) table with each intervention option (ie, intervention and control) in one column and province of residence (ie, New Brunswick, Nova Scotia, and Prince Edward Island) in another column. We wanted to ensure that an equal number of participants were randomized to the intervention and control group within each province in a balanced manner. Therefore, there were 6 study options uploaded to the software. Once the allocation table was uploaded to REDCap, it was locked and could not be modified.

REDCap will be used to randomize the participants. After a participant has completed the baseline surveys, the researcher will press the “randomize” button to determine the participant’s group allocation. While assignment to the groups is random, once assigned, participants are not blinded to their group. The researcher will inform each participant of the group they are allocated to at the end of the baseline interview. The research staff (research coordinator and research assistant) will be responsible for screening, consenting, enrolling, and using Recap’s randomization module to allocate participants to their study group.

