Organizations were asked if they would be interested in partnering with the study by appointing a staff member who could serve as a facilitator on the project. Organizations were notified that the facilitators would need to take part in a 2-hour training session on how to deliver the intervention and would be assigned the tasks of recruiting potential participants and delivering the intervention to any participants that they recruited within their organization. Organizations were informed that they would receive a stipend of CAD $2500 (CAD $1=US $0.74) for agreeing to partnership 1 and having a staff member take part in the training and recruiting and delivering the intervention to 1 to 5 participants. An additional CAD $2500 stipend will be offered to any organization that has a facilitator who recruits and delivers the intervention to ≥6 participants, given the increased time and resources this would take. A technology fee of CAD $1000 will be provided to each partnering organization for overhead costs and the use of their equipment (ie, laptops and phones) to deliver the intervention. Organizations were notified that staff members need to meet the following criteria to be eligible to become a facilitator: (1) at least 2 years of experience working in the IPV service delivery field and (2) completion of a postsecondary education program (eg, social work, health professions, human services, counseling, health promotion, or social sciences).

The research team also hired staff facilitators throughout the Maritime provinces to deliver the intervention to participants that were not recruited from within community-based organizations. The staff facilitators will be completing the same tasks but will be working independently (ie, not with an organization). All staff facilitators need to meet the minimum educational and experience requirements.

#### Partnership 2

We offered a CAD $500 honorarium to organizations that were willing to help us out with participant recruitment only. The research team asked partnering organizations if they could help with recruitment by distributing the recruitment poster to potential participants and completing 1 of the following tasks: (1) asking potential participants within their organizations for permission for a member of the research team to contact them and (2) share information about the study with potential participants who can contact the research team directly if they wish to do so.

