### Outcomes Measured

Research staff will collect quantitative effectiveness data from participants by telephone or video call at 3 time points: baseline, 3 months, and 9 months. Research staff will schedule a meeting by telephone or Zoom (Zoom Video Communications) to collect the survey responses from participants verbally. Table 1 details the survey information to be collected directly from participants.

**Table 1 table1:** Quantitative measures.

Quantitative measure collected	Time point for data collection			Explanation
	Baseline	3 months	9 months	
Screening questions	✓			Age, province of residence, and description of the stage of their relationship with their abusive partner
Demographic information	✓			Education, marital status, and diversity characteristics (eg, immigrant status, francophone status, ethnic status, and rural status)
WEB^a^	✓	✓	✓	To measure women’s experiences of feeling fearful and controlled by their abusive partner [43]
DCS^b^	✓	✓	✓	To measure the conflict (ie, difficulty) that women endure in making decisions about leaving their abusive relationship [44]
IPV^c^ strategies index	✓	✓	✓	To measure the different types of IPV strategies that women are using to keep themselves safe in their abusive relationship [45]
SF-12v2^d^	✓	✓	✓	To measure quality of life [46]
CES-D^e^	✓	✓	✓	To measure depressive symptoms [47]
ISEL^f^	✓	✓	✓	To measure perceived social support [48]

^a^WEB: Women’s Experiences of Battery Scale.

^b^DCS: Decisional Conflict Scale.

^c^IPV: intimate partner violence.

^d^SF-12v2: Short Form Health Survey.

^e^CES-D: The Center for Epidemiologic Studies Depression Scale.

^f^ISEL: The Interpersonal Support Evaluation List.

Primary outcomes include (1) physical and mental health, (2) knowledge about IPV, and (3) safety strategies. Physical and mental health will be assessed using the following scales: Short Form Health Survey [46], Centre for Epidemiologic Studies Depression Scale [47], and Interpersonal Support Evaluation List [48]. Knowledge about IPV and safety strategies will be measured using the following scales: the Women’s Experiences of Battery Scale [43], Decisional Conflict Scale [44], and Intimate Partner Violence Strategies Index [45].

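### All six primary scales are taken verbally by staff whose roles also randomise women and announce the arm, so interviewer bias is unguarded and allocation concealment is not assured

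*Protocol article*

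**What the plan says.** Random Assignment of Interventions covers the allocation. "The research coordinator developed an allocation table that included each option for random assignment that was stratified by the province of residence". The same section states that "The random allocation sequence was generated using REDCap" and, of the table, that "Once the allocation table was uploaded to REDCap, it was locked and could not be modified". The arm is released only when the baseline surveys are complete, and the researcher tells the woman her group at the end of that interview. The staffing is explicit: "The research staff (research coordinator and research assistant) will be responsible for screening, consenting, enrolling, and using Recap’s randomization module".

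Outcomes Measured covers the follow-up: "Research staff will schedule a meeting by telephone or Zoom (Zoom Video Communications) to collect the survey responses from participants verbally". It names six scales under the primary outcomes: SF-12v2, CES-D, ISEL, WEB, DCS and the IPV Strategies Index. Data Management has the coordinator and the assistants enter the answers at baseline and both follow-ups, and gives REDCap access to these staff only.

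Trial Design declares the trial unblinded. Limitations lists generalisability and self-report.

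**The concern.** Two separate protections depend on who does what.

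The first is outcome collection. The scales cover fear, depressive symptoms, perceived support, decisional conflict, quality of life and safety strategies. An interviewer who reads the items aloud and knows the arm can affect the answers through tone, prompting or the coding of a hesitant reply. If this happens differently by arm, it enters the between-group comparison directly, and it can do so on every primary scale.

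The second is concealment. Someone who knows the coming assignment can, even without intending to, judge eligibility or time an enrolment differently. The person who developed the table is also one of those who decide on eligibility and entry.

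**Working it through.** The article states no figure on this point, so there is none to reproduce. The check sets the roles side by side and then gives two short calculations.

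**Roles, as stated**

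| Task | Who | Section |
|---|---|---|
| Develop the allocation table | Coordinator | Random Assignment of Interventions |
| Screen, consent, enrol, randomise | Coordinator and assistant | Random Assignment of Interventions |
| Tell the woman her arm | The researcher at the baseline interview | Random Assignment of Interventions |
| Stay in contact with facilitators | Coordinator | Training for Facilitators; Data Monitoring |
| Take the scales verbally at 3 and 9 months | Research staff | Outcomes Measured |
| Enter the answers; hold REDCap access | Coordinator and assistants | Data Management |
| Invite AIM women to a qualitative interview at 9 months | Coordinator | Qualitative Component |

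The coordinator appears in nearly every row, and no role is kept apart from allocation. This is an overlap of roles. The article does not say that the individual who announced a woman's arm also interviews her later.

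**Concealment safeguards, one by one**

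- Generation in REDCap would conceal the order if REDCap alone fixed it. The text then describes an Excel table developed by the coordinator and uploaded, so it is unclear whether that table was the ordered sequence or only a list of the arm-by-province options.
- The lock prevents later changes. It does not remove what the table's author already knew.
- Release after baseline hides the arm from anyone who does not already know it.

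**Follow-up dates can reveal the arm**

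Participant Involvement by Group counts follow-up from the final support session in the AIM arm and from baseline in the comparison arm. Take 3 months as 52 × 3/12 = 13 weeks, 9 months as 52 × 9/12 = 39 weeks, and the calls as about 12 weeks, with no delay before they start.

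- Comparison arm: about 13 and 39 weeks after baseline.
- AIM arm: about 12 + 13 = 25 and 12 + 39 = 51 weeks after baseline.

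The gap is about 12 weeks at each visit. Whoever schedules the visit must know the arm, and an interviewer who sees the baseline date can work it out.

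**Illustration of size (assumed shifts)**

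Inputs: 30 per arm (Sample Size). Assumed: two-sided 5% level, normal approximation, one scale at one time point, no true effect, and a differential reporting shift of d standard deviations. The standard error in SD units is √(2/30) = 0.258. The rejection rate is Φ(d/0.258 − 1.96) + Φ(−d/0.258 − 1.96).

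| d (SD) | Rejection rate |
|---|---|
| 0 | 5.0% |
| 0.1 | 6.7% |
| 0.2 | 12.1% |
| 0.3 | 21.3% |
| 0.5 | 49.1% |

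Nothing in the documents says which row applies, or in which direction a shift would go.

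**The case against.** The trial is openly declared unblinded and self-report is a stated limitation. All six scales are answered by women who know their arm, so a masked interviewer would remove only the interviewer's share of any bias. That stands, and it limits what the fix can achieve. It does not remove the point, because leaving participants unmasked does not require unmasked interviewers.

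It can also be said that block sizes and access rights are usually left to the full protocol. That stands too. The point does not rest on their absence, but on the roles that the article assigns.

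A reader might infer three stronger things that the documents do not support:

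- **That concealment is absent.** The same section states three safeguards. They leave a gap but are not nothing.
- **That allocation ran in pairs and was predictable.** The text says "Therefore, there were 6 study options uploaded to the software", which is two arms by three provinces. No block size is given, and six literal rows would serve only two women per province, so they cannot be the whole table. Any guessing rate would rest on an assumption.
- **That the stipend is a motive to steer allocation.** The further payment goes to an organisation with a "facilitator who recruits and delivers the intervention to ≥6 participants", so it does depend on delivery. But organisations and their facilitators do not screen or randomise, and no such payment to research staff is described.

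**Conclusion.** The point holds in two parts of unequal strength. The firmer part is that follow-up collection of all six primary scales is open to interviewer bias, since the roles that randomise and announce the arm also conduct the interviews and no masking is described. Limitations does not mention it. The weaker part is that concealment is not assured, because the table's author also enrols and the text leaves open whether that person knew the order.

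The documents do not fix the size. On the assumed shifts, modest differential reporting would be enough to matter in a trial with 30 women per arm, but this shows sensitivity and is not an estimate of bias. The conclusion rests on the roles as written; if individuals were in fact kept apart, saying so would largely settle the first part. This is a worthwhile, inexpensive improvement. It does not show that the allocation was compromised.

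**What to change.** Split the existing roles for the remaining 3- and 9-month interviews.

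- The coordinator handles randomisation, arm notification, facilitator contact and the scheduling of follow-ups. Scheduling has to sit there because visit timing differs by arm.
- A research assistant conducts the interviews without REDCap access to the allocation field or baseline dates, and without access to session records. Facilitators document sessions on OneDrive, so rights need restricting there as well.
- That assistant should not be the one who randomised the woman. Where this cannot be arranged, record the interview as unmasked.
- The assistant asks each woman at the start not to reveal her group, and records any unmasking.
- The coordinator makes the 9-month qualitative invitation separately, after the scales are recorded.

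Report as limitations the interviews already taken unmasked, the remaining unmasking through participants, and the enrolling role of the table's author. State who fixed the order of the sequence and who could view it.

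The cost is a change of user rights, some reassignment and less flexible scheduling. Data Management refers to assistants in the plural, but Random Assignment of Interventions names only one; with a single assistant, masking would reach only women whom that assistant did not randomise. The locked table and the payment terms already given to organisations can stay as they are: changing either during the trial has its own cost, and this point does not need it.

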### Outcomes Measured

Research staff will collect quantitative effectiveness data from participants by telephone or video call at 3 time points: baseline, 3 months, and 9 months. Research staff will schedule a meeting by telephone or Zoom (Zoom Video Communications) to collect the survey responses from participants verbally. Table 1 details the survey information to be collected directly from participants.

**Table 1 table1:** Quantitative measures.

Quantitative measure collected	Time point for data collection			Explanation
	Baseline	3 months	9 months	
Screening questions	✓			Age, province of residence, and description of the stage of their relationship with their abusive partner
Demographic information	✓			Education, marital status, and diversity characteristics (eg, immigrant status, francophone status, ethnic status, and rural status)
WEB^a^	✓	✓	✓	To measure women’s experiences of feeling fearful and controlled by their abusive partner [43]
DCS^b^	✓	✓	✓	To measure the conflict (ie, difficulty) that women endure in making decisions about leaving their abusive relationship [44]
IPV^c^ strategies index	✓	✓	✓	To measure the different types of IPV strategies that women are using to keep themselves safe in their abusive relationship [45]
SF-12v2^d^	✓	✓	✓	To measure quality of life [46]
CES-D^e^	✓	✓	✓	To measure depressive symptoms [47]
ISEL^f^	✓	✓	✓	To measure perceived social support [48]

^a^WEB: Women’s Experiences of Battery Scale.

^b^DCS: Decisional Conflict Scale.

^c^IPV: intimate partner violence.

^d^SF-12v2: Short Form Health Survey.

^e^CES-D: The Center for Epidemiologic Studies Depression Scale.

^f^ISEL: The Interpersonal Support Evaluation List.

Primary outcomes include (1) physical and mental health, (2) knowledge about IPV, and (3) safety strategies. Physical and mental health will be assessed using the following scales: Short Form Health Survey [46], Centre for Epidemiologic Studies Depression Scale [47], and Interpersonal Support Evaluation List [48]. Knowledge about IPV and safety strategies will be measured using the following scales: the Women’s Experiences of Battery Scale [43], Decisional Conflict Scale [44], and Intimate Partner Violence Strategies Index [45].

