### AIM Intervention

#### Overview

After completing a recent systematic review focused on the IPV interventions relevant to women during the COVID-19 pandemic, including research evidence from 4 systematic reviews and 20 individual studies [27], our team identified an advocacy health promotion program [34] that was ideal to adapt, implement, and test in this RCT. Given that the advocacy health promotion program is not a proprietary program, permission was not required to adapt it for our research. The intervention reported by Tiwari et al [34] has been selected to be adapted for this trial because the researchers reported that it significantly reduced depression and psychological aggression scores and improved perceived social support and the use of safety-promoting behaviors. Other interventions that we examined in our systematic review either did not result in positive outcomes for the health and safety needs of women or the results did not reach statistical significance. We also found that providing highly tailored interventions can contribute to positive outcomes [35,36], and the intervention reported by Tiwari et al [34] could be tailored as needed. This study will pay particular attention to ensuring that those who are trained to deliver the intervention provide individualized and person-centered support.

An innovative aspect of this research is the adaptation of the intervention to meet the needs of midlife and older women that can often be different from those of younger women. For example, leaving one’s home, property, and community may not be a priority for older women experiencing IPV [19], and therefore, the women will be provided support to empower them to identify their own goals and strategies for achieving those goals. The intervention has also been adapted to meet the needs of women who reside in the Maritime provinces of Canada. Information on local IPV services and resources will be provided to the participants. The format will also be adapted to meet the preferences of the women to use whatever form of technology they prefer for the social support component of the study. In addition, those trained to deliver the program will use a person-centered perspective to support the unique needs of the participants, such as for participants who are francophone, living in a rural place, or a new immigrant to Canada.

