### Statistical Analysis

Quantitative data will be exported from REDCap as a spreadsheet and then uploaded into SPSS (IBM Corp) for quantitative analysis. Participants in the AIM intervention group need to complete the empowerment component and attend at least 10 out of 12 weekly calls of the social support component for their quantitative data to be included in the analysis.

Descriptive statistics will provide a profile of study participants, including demographics for the whole sample and for those in each of the 2 groups. The provisional effect of the intervention will be tested using a prospective chi-square test of independence between the 2 groups for categorical data (Fisher exact test) at 3 and 9 months. Repeated measures analysis of variance will measure mean differences between the groups on continuous variables at 3 and 9 months.

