### Dissemination of Results

The findings of this study will be disseminated in several ways. We will submit a journal article to a peer-reviewed journal (eg, *Journal of Women and Aging* and *Violence Against Women*). We will ensure that the article is open access to ensure accessibility. We will deliver conference presentations at academic and professional conferences (eg, Canadian Association on Gerontology Annual Conference and Canadian Domestic Violence Conference). The intended audience will be researchers, practitioners, students, trainees, and policy makers. We will also develop and disseminate other research outputs that are required by the funders (eg, plain language summary, brief video, and infographic) in English and French. These accessible documents will be important for all our team members to share with their networks.

If the AIM intervention is determined to be effective, we will use the feedback we receive from the qualitative interviews with staff and participants to refine the staff training program and make it publicly available in both French and English. The final program materials will be distributed to service providers who work with victims of IPV and elder abuse in the Maritime provinces. In addition, the final program will be made freely available to anyone interested in supporting midlife and older women experiencing IPV and will be posted and publicized in the resources section of the Muriel McQueen Fergusson Centre for Family Violence Research website. The program will also be posted and distributed through the resource hub of the Canadian Network for the Prevention of Elder Abuse.

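### No scale, time point or success rule is singled out among three primary domains, six scales and two follow-ups, although release of the programme depends on a finding of effectiveness

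*Protocol article*

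**What the plan says.** The section Outcomes Measured states "Primary outcomes include (1) physical and mental health, (2) knowledge about IPV, and (3) safety strategies". The first domain is assigned three scales (SF-12v2, CES-D, ISEL). The other two domains share three more (WEB, DCS and the IPV Strategies Index), with no indication of which scale serves which domain. Table 1 collects all six at baseline, 3 months and 9 months. Apart from screening and demographic items it lists no other measure, so every outcome scale belongs to a primary domain. Anticipated Principal Findings again names all three domains as primary.

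Statistical Analysis plans that "Repeated measures analysis of variance will measure mean differences between the groups on continuous variables at 3 and 9 months". For categorical variables, "The provisional effect of the intervention will be tested using a prospective chi-square test of independence between the 2 groups for categorical data", also at both visits. It does not say which variables are categorical, and it puts neither visit first.

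Objectives describes the trial as a test of effectiveness. Dissemination of Results makes distribution of the final programme follow a condition: "If the AIM intervention is determined to be effective". Nothing says which result, or how many, would meet it. On the other side, Statistical Analysis calls the tested effect provisional, and Conclusions calls the quantitative evidence preliminary.

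**The concern.** A trial that sets out to test effectiveness, and attaches a decision to the answer, needs to say in advance which comparison gives the answer. Here at least a dozen could. If one of six scales crosses a threshold at one of two visits, the text does not say whether AIM has been shown to work, and nothing in the article prevents that scale from becoming the headline.

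The trial is small (70 women recruited, with 30 per arm expected to remain), so an isolated significant result is weak evidence. It is also unblinded, and Results says analysis runs alongside data collection. The chance to favour a scale or visit after seeing data is therefore real unless the choice is fixed first.

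**Working it through.** **The plan's own figure.** There is none to reproduce. The article states no significance level, power or overall error rate.

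**Inputs from the article**
- Scales assigned to primary domains: 3 + 3 = 6 (Outcomes Measured).
- Follow-up visits compared: 2 (Statistical Analysis; Table 1).
- Scale-by-visit comparisons: 6 × 2 = 12.
- Women per arm after attrition: 30 (Sample Size).

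**Assumptions, none stated in the article**
- Each comparison is tested at two-sided 0.05 with no multiplicity adjustment.
- Any one significant result counts.
- There is no true effect on any scale.
- Scales are oriented so that positive values favour AIM, and test statistics correlate at 0 to 0.7 between scales and between visits. Across different scales at different visits, the correlation is the product of the two.

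**Independent tests**
- Either direction, 12 tests: 1 − 0.95^12 = 0.460.
- Favouring AIM, 12 tests: 1 − 0.975^12 = 0.262.
- Either direction, 6 tests: 1 − 0.95^6 = 0.265.
- Favouring AIM, 6 tests: 1 − 0.975^6 = 0.141.

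**Correlated tests** (multivariate normal simulation, 200,000 draws per setting)

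| Tests | Correlation, scales / visits | Any difference, either direction | At least one favouring AIM |
|---|---|---|---|
| 1 | – | 5.0% | 2.5% |
| 12 | 0 / 0 | 46.0% | 26.2% |
| 12 | 0.3 / 0.5 | 40.1% | 20.8% |
| 12 | 0.5 / 0.7 | 32.4% | 16.2% |
| 12 | 0.7 / 0.7 | 26.0% | 13.1% |
| 6 | 0 | 26.5% | 14.1% |
| 6 | 0.5 | 20.7% | 10.3% |
| 6 | 0.7 | 16.6% | 8.3% |

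The 6-test rows apply if repeated measures ANOVA gives one between-arm test per scale. The 12-test rows apply if the arms are compared separately at each visit. The wording allows either.

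**Why naming one comparison is better than correcting twelve.** With 30 per arm and an assumed standardised difference of 0.5, power = Φ(0.5 × √(30/2) − z).
- At 0.05: Φ(1.94 − 1.96) = 49%.
- At Bonferroni 0.05/6 = 0.0083: 24%.
- At Bonferroni 0.05/12 = 0.0042: 18%.

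A correction over all scales and visits would control the error rate but leave little power at this sample size.

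**The case against.** The strongest reply has four parts.

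1. **An adjustment may sit in an analysis plan that is not shown.** This stands, so the absence of a multiplicity method is not the point here. Choosing the primary outcome is protocol content, though, and the article does choose: it makes everything primary. An adjustment elsewhere would not by itself say which result makes AIM effective.

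2. **A reader might infer that the chance of a false claim of effectiveness is 32% to 46% instead of 5%.** The article does not support that. Those percentages count differences in either direction, and a scale that significantly favours the comparison group is no claim that AIM works. The matching figures are 16% to 26% against 2.5%. The article also states no alpha, gives no correlations, plans an analysis that may yield only one test per scale, and nowhere says that one significant scale is enough. Anticipated Principal Findings expects benefit across all three domains.

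3. **The language is partly exploratory.** The effect is called provisional, the evidence preliminary, and Directions for Future Research asks for a further study, preferably pan-Canadian. This is fair mitigation. It conflicts, however, with an objective of testing effectiveness and with a distribution step conditional on effectiveness.

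4. **Choosing CES-D would be a reviewer's preference.** Agreed. The Overview of the AIM Intervention says the source programme "significantly reduced depression and psychological aggression scores" and also improved perceived social support and safety behaviours. Several scales could be justified, and the choice is the sponsor's.

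**Conclusion.** The point holds as a design defect. Six scales at two visits are all primary, none is singled out, and the condition for releasing the programme has no defined test. This rests on the text alone.

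Its size is conditional. With 12 unadjusted two-sided 0.05 tests and any one counting, the chance of at least one false-positive difference is about 32% to 46%, from scale correlation 0.5 with visit correlation 0.7 up to independence; it is 26% if both are 0.7. The chance of one favouring AIM is about 16% to 26% (13% if both are 0.7). With one test per scale and correlation from 0.7 to 0, the figures are 16.6% to 26.5% in either direction and 8.3% to 14.1% favouring AIM. Even the lowest favourable figure, 8.3%, is more than three times the 2.5% of a single test. The percentages should not be read as the trial's actual error rate, because alpha, correlations, adjustment and success rule are all unstated.

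**What to change.** Before any between-arm comparison is looked at:

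1. **Name one primary scale.** The choice is the sponsor's. CES-D is one example, since reduced depression is among the reasons given for adopting the source programme.
2. **Name one primary time point, at the same interval from randomisation in both arms.** Participant Involvement by Group now counts follow-up from the final support session for AIM and from baseline for the comparison group. With 12 weekly calls delivered on schedule, the AIM women's first follow-up falls roughly three months later after randomisation than the comparison group's. A sole decision test placed on the 3-month visit as now defined would inherit that mismatch.
3. **Make the other five scales and the other time point secondary**, reported as estimates with 95% confidence intervals.
4. **Define the release condition** in Dissemination of Results as success on the primary comparison, and state the significance level.
5. **Record when the choice was made and whether any comparison by arm had been seen**, because Results has analysis continuing during data collection.

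If the trial is meant only to give preliminary evidence, the alternative is to say so in Objectives and remove the effectiveness trigger from Dissemination of Results.

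The cost of items 1, 3, 4 and 5 is protocol and registry wording. Item 2 may also require rescheduling visits, or using the visit whose timing can be matched. The statistical price is fewer outcomes on which a confirmatory claim can be made.
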